### Contamination

Using clusters as a unit of randomisation and maintaining a 3 km travel distance between clinics should minimise the risk of contamination. However, there is a theoretical possibility of some contamination if PLWHA in the ExtraCECI arm was to meet with PLWHA in the standard HIV care arm and then divulge information about intervention components. To minimise the possibility of any form of contamination, participants in both clusters will be asked if they visited any health facility since the last appointment. We will request those in the ExtraCECI (intervention group) to refrain from sharing study-related information and materials during the study. We will also ask those in the standard HIV care arm if they had any contact with any participant from the ExtraCECI arm.

### Data management

Data management will be in accordance with the General Data Protection Regulation (GDPR)^47^ and Ghana Data Protection Act 2012.^48^ Each site and participant will be assigned a unique trial identification number at the start of data collection. A record sheet linking patient details and identification number for participants including consent forms will be kept at each site in a securely locked filling cabinet, separate from datasheets.

Quantitative outcome data will be collected using paper-based questionnaire booklets for each participant, and the hard copies of the assessments will be stored securely at clinic sites or where possible inside a locked cabinet at a secured office at the University of Ghana (UoG). Each participant CRF booklet data will be entered into Qualtrics (online version), hosted by the UK Clinical Trials Unit. The in-country data manager will audit the data entry process. The resulting database will only be accessible by the team at the Clinical Trials Unit, who will query the data entered by sites as well as checking for completeness and consistency. Data sharing agreements will be put in place for the transfer, storage, restricted access and disposal of personal information in accordance with GDPR,^47^ Ghana Data Protection Act 2012,^48^ Clinical Trials Unit Standard Operating Procedures (SOP) and Good Clinical Practice (GCP) regulations.

### Statistical and effectiveness analysis

Analyses will be undertaken in Stata V.18 (or later) based on two-sided 5% significance levels under the principles of intention-to-treat, as detailed in a statistical analysis plan. Baseline data will be summarised descriptively by treatment group using means and SD or median and IQR for continuous variables and counts and percentages for categorical variables. Participants' MOS-HIV scores will be analysed using a repeated measures linear mixed effects model. The model will include MOS-HIV scores as outcome, with fixed effect of treatment by time interaction, adjusting for important baseline variables (including stratification factors) and random effect of clinic. Time points will be nested within patients and modelled using a covariance structure. Different structures will be considered and the simplest structure with the best fit (assessed using Bayesian Information Criterion) will be used. Model assumptions of normality of standardised residuals will be assessed (using Q-Q plots) in addition to homoscedasticity (using a scatter plot of standardised residuals against fitted values). If the assumptions are not met, relevant transformations of MOS-HIV scores and non-parametric tests will be considered. The treatment effect at the time points will be extracted in the form of an adjusted mean difference, 95% CI and p value (with the primary being at 12 months). Analysis of the primary outcome will be checked by a second statistician in accordance with clinical trials unit SOPs (Primary Analysis Sign Off Form) before results are circulated to wider members of the trial team. Continuous secondary outcomes will be similarly analysed using a similar model to the primary analysis.

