**Methods and analysis:**

This cRCT will randomly assign 26 recruited HIV clinics using 1:1 allocation to either ExtraCECI intervention or standard HIV care, with each clinic recruiting an average of 25 participants, that is, 650 in total. Eligible participants are adult PLWHA aged at least 18 years and in HIV care for at least 6 months, with cognitive ability to consent as guided by the Mental Capacity Act, clinically well to participate, attending an outpatient clinic. Healthcare professionals (HCP) at clinics randomised to the ExtraCECI intervention arm will receive training on person-centred care and holistic assessment of PLWHA in the domains of physical, psychological, social and spiritual well-being. PLWHA will be empowered to contribute to their care decisions including HCP using telehealth for ExtraCECI delivery with ongoing mentorship, while participants in the Standard HIV Care arm continue with usual care. The primary outcome is quality of life measured at the individual level using Medical Outcomes Study-HIV (MOS-HIV). The primary analysis will compare MOS-HIV total scores between groups using repeated measure linear mixed model and adjusting for important baseline characteristics (including stratification factors) and random effect of clinic. The incremental cost-effectiveness ratio will be used to estimate the cost-effectiveness of the ExtraCECI intervention, and a process evaluation will be conducted.

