### Sample size

As there is no widely established minimal clinical important difference for the Medical Outcomes Study-HIV (MOS-HIV) measure, we followed best practice guidelines^40^ using a standardised effect size approach. We estimated that an average cluster would be 20, but there would be variation in this estimate, which we incorporated in the sample size (coefficient of variation).^41^ No clinic level intracluster correlation coefficient (ICC) is available, and the feasibility trial conducted was too small to reliably estimate the ICC, hence we chose a value of 0.04.^42^ Therefore, for 90% power to detect a minimum effect size of 0.4 in the MOS-HIV, a total of 650 PLWHA would need to be randomised from 26 clinics, assuming an ICC of 0.04, average cluster size of 25 with 20% loss to follow-up.

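### As described, the primary model holds each clinic's effect constant over time while the primary contrast is at 12 months, so its standard error is understated if clinic effects shift between visits and clinic variance does not fall

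*Protocol article*

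**What the plan says.** The section on statistical and effectiveness analysis describes a linear mixed model for repeated MOS-HIV scores "with fixed effect of treatment by time interaction, adjusting for important baseline variables (including stratification factors) and random effect of clinic". The abstract repeats the clinic term: "adjusting for important baseline characteristics (including stratification factors) and random effect of clinic". The next statement in the analysis section deals with time: "Time points will be nested within patients and modelled using a covariance structure". The choice between candidate structures by BIC follows directly and concerns that within-patient structure. Treatment effects are extracted at each time point, and the 12-month one is primary. Tests are "based on two-sided 5% significance levels under the principles of intention-to-treat".

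No clinic-by-time random effect, clinic-level slope or robust standard error is mentioned. The article refers to a statistical analysis plan, which is not shown.

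The sample size section plans "for 90% power to detect a minimum effect size of 0.4 in the MOS-HIV". It says of the ICC, which could not be estimated, "hence we chose a value of 0.04", and it assumes an "average cluster size of 25 with 20% loss to follow-up". It gives no correlation between clinic effects at different visits.

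**The concern.** A clinic effect that is constant over time makes two patients of one clinic as strongly correlated when one is measured at T1 and the other at T5 as when both are measured at T5. If clinic effects move between visits, that is not so. The fitted clinic variance is then close to the variance of a clinic's average effect over the visits, which is smaller than the clinic variance at any one visit when that variance is stable. The part of the clinic effect specific to a visit is pushed into the patient-level variance, where it is divided by the number of patients per clinic and nearly disappears from the standard error.

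This matters because the primary estimate is a single-visit contrast and needs the clinic variance at 12 months. The trial gives some reason to expect movement: staff are trained, practise for about four weeks and receive continuing mentorship, and fidelity of delivery is one of the questions for the process evaluation. At stake are the width of the primary confidence interval and the type I error of the primary test.

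**Working it through.** **Inputs from the protocol article.** Two-sided 5%; 90% power; effect 0.4 SD; ICC 0.04; 26 clinics, 13 per arm; 25 recruited per clinic with 20% loss, so m = 20 analysed; five visits after randomisation (T1 to T5).

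**Assumptions, not in the documents.** Total variance 1 at each visit; equal clinic sizes; no covariates; clinic autocorrelation r (the correlation of a clinic's effects at two different visits) from 0.2 to 1, the same for every pair of visits.

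**Step 1: the plan's own figure.** Without clustering, the total is 2 × 2 × (1.960 + 1.282)² / 0.4² = 262.7. On cluster size the article says "there would be variation in this estimate, which we incorporated in the sample size (coefficient of variation" but does not print the coefficient of variation. With m = 20 and an assumed coefficient of 0.5, the design effect is 1 + (1.25 × 20 − 1) × 0.04 = 1.96. With m = 25 and no variation it is 1 + 24 × 0.04 = 1.96 as well. Then 262.7 × 1.96 = 514.9, and 514.9 / 0.8 = 643.6, or 25.7 clinics of 25. This rounds up to 26 clinics and 650 participants, so the stated size is reproduced. It rests on the clinic variance at a single visit.

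**Step 2: the true standard error at 12 months.** √[(2/13) × (0.04 + 0.96/20)] = √[(2/13) × 0.0880] = 0.1164 SD. This holds for any r, because only one visit enters.

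**Step 3: what the one-effect model estimates.** In this balanced layout with compound symmetry within patients, REML gives in expectation:

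- clinic variance: 0.04 × [r + (1 − r)/5], the variance of the clinic's mean effect over five visits;
- amount moved into the patient-level variance: 0.8 × 24 × 20 × 0.04(1 − r) / 518, where 24 is the between-clinic degrees of freedom, 518 = 26 × 19 + 24, and 0.8 = 4/5.

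Example at r = 0.6. The clinic variance is 0.04 × 0.68 = 0.0272. The amount moved is 0.8 × 480 × 0.016 / 518 = 0.0119. The model standard error is √[(2/13) × (0.0272 + 0.9719/20)] = √[(2/13) × 0.0758] = 0.1080. The ratio to the truth is 0.1080 / 0.1164 = 0.928. The size of a nominal 5% z-test is 2 × [1 − Φ(1.96 × 0.928)] = 6.9%.

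| r | fitted clinic variance | model SE | ratio to 0.1164 | z-test size |
|---|---|---|---|---|
| 1.0 | 0.0400 | 0.1164 | 1.000 | 5.0% |
| 0.9 | 0.0368 | 0.1143 | 0.983 | 5.4% |
| 0.8 | 0.0336 | 0.1122 | 0.965 | 5.9% |
| 0.6 | 0.0272 | 0.1080 | 0.928 | 6.9% |
| 0.4 | 0.0208 | 0.1035 | 0.890 | 8.1% |
| 0.2 | 0.0144 | 0.0989 | 0.850 | 9.6% |

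**Step 4: does the within-patient structure repair it?** No. A numerical REML fit with an unstructured patient covariance gives the same standard errors to four decimals (0.1122 at r = 0.8, 0.1058 at r = 0.5). With AR(1) data and an AR(1) fit the ratios are 0.971 and 0.925. If the clinic correlation decays with the gap between visits, the shortfall is larger: the ratio is 0.93 to 0.94 at a lag-1 correlation of 0.8 and 0.87 at 0.5.

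**Step 5: clinic variance that changes over time.** If it rises from 0.02 at T1 to 0.06 at T5, the ratio is 0.865 at r = 0.8 and 0.82 at r = 0.5 (z-test size about 9% and 11%). If it falls from 0.06 to 0.02, the true 12-month standard error is √[(2/13) × 0.068] = 0.1023 and the model's is 0.1115 at r = 0.8 and 0.1053 at r = 0.5 under compound symmetry. The ratios are 1.09 and 1.03, so the standard error is too large.

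**Step 6: simulation.** Two sets of runs agree in direction but scatter. One, with an unstructured patient covariance, rejected in 5.7%, 5.1%, 7.3% and 8.1% of trials at r = 1, 0.8, 0.6 and 0.4 (Monte Carlo error about ±1.2 points). The other, with compound symmetry, gave 5.5%, 7.5%, 8.7% and 12.3% at r = 1, 0.8, 0.5 and 0.2. At r = 0.8 simulation does not settle the size of the excess.

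**The case against.** The strongest reply is that an article condenses the protocol. It says random effect without saying intercept, excludes nothing, and defers to an analysis plan that may add the missing term. This stands as far as a reader might infer that a clinic-by-time term has been ruled out; the text does not support that. But the article does more than stay silent. It names the clinic term, assigns the correlation over time to patients, ties the BIC search to that structure and fixes the primary time point. Followed as written, that is a clinic effect constant over time.

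A reader might also infer that the 12-month standard error is too small whenever clinic effects shift, so that the primary p value is anti-conservative in general. The documents do not support this either. At autocorrelation 1 with stable clinic variance the model is correct, and in the falling-variance example the standard error was too large.

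The size rests on an assumption. No autocorrelation is given, and the sample size section says that not even the ICC could be estimated reliably. At 0.9 the effect is minor. The calculation also leaves out baseline adjustment and unequal clinic sizes, so the percentages do not carry over exactly.

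Finally, the sample size is not at fault. An ICC for one visit is the right basis for a 12-month contrast, and 650 is reproduced. The reference distribution for the test is not stated, which an article may leave to the analysis plan; a normal reference cannot be read into it.

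**Conclusion.** The concern holds in conditional form. As described, the model cannot represent clinic effects that change between visits, and the primary contrast is the kind of estimate for which this matters. If clinic effects are imperfectly correlated across visits and clinic variance is stable or rising, the 12-month standard error is understated under every within-patient structure examined. With stable clinic variance and equal correlation between visits, the shortfall runs from about 2% (autocorrelation 0.9) to 11% (0.4). That is minor at the upper end and material at about 0.6 and below. The direction is not guaranteed if clinic variance falls towards 12 months. Because the size cannot be known before the data, the model should allow for it rather than assume it away.

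**What to change.** Add a clinic-by-visit random effect to the primary model, that is, clinic-level effects for each visit with an exchangeable covariance. Keep the planned BIC selection for the within-patient covariance, since replacing it would not cure the problem. Test the 12-month effect with a small-sample correction based on between-clinic degrees of freedom (26 − 2 = 24, less any clinic-level covariates). State this in the statistical analysis plan before unblinded data are seen, or confirm there that it is already planned.

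With 26 clinics the added variance may be estimated at or near zero, or the model may fail to converge. Prespecify the fallback, for example a clinic-level analysis of the 12-month scores. An exchangeable structure assumes the same clinic variance at every visit, so it does not fully cover a variance that rises or falls; that clinic-level analysis could also serve as a sensitivity check.

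The sample size does not change, because it already uses the single-visit ICC of 0.04. The cost is one added term, slightly wider confidence intervals and the fallback rule. If clinic effects prove stable, little is lost.

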### Cost-effectiveness evaluation

We will adapt an existing costing measure for the economic evaluation of ExtraCECI from HCP perspective and reported by the Consolidated Health Economic Evaluation Reporting Standards (CHEERS) 2022 checklist.^49^ The effectiveness will be determined by self-reported QoL in the MOS-HIV measurements (descriptions) and valuations (utilities). For QoL measurements, the overall mean scores and scores for each domain of the MOS-HIV will be calculated. Analysis will be carried out to determine the difference between the overall mean scores of each in the subgroups of treatment (intervention and control).

Cost data will be collected from all the HIV study clinics (intervention and control) on activities associated with HIV management as well as the intervention-specific activities. This will require taking inventory of all resources in the facilities and then allocate these costs to HIV management cost centre, using CHEERS 2022 checklist,^49^ to guide the data collection and analysis. A 1-year time horizon will be applied for both cost and effectiveness. We will use standard microcosting techniques, incorporating a full costing approach, with both recurrent costs, overhead items and capital costs.

We will annualise capital costs at a discount rate of 3% per year, and according to the useful life of each item.^50^ The total economic costs of ExtraCECI will be estimated and then categorised into preintervention, intervention and indirect costs. The incremental cost-effectiveness ratio, for the estimation of the cost-effectiveness, will be expressed as the ratio of the difference in cost to the difference in effect (QoL) between ExtraCECI versus standard HIV care. Furthermore, a Budget Impact Analysis will be conducted to gauge the impact of the intervention on governmental health expenditure.^51^

One-way sensitivity analysis will be conducted to determine whether changes in variables (discount rate and life expectancy of equipment) and PLWHA utilisation of ExtraCECI will change the economic costs or cost-effectiveness of the implementation. Accordingly, the discount rate will be varied from 3% to 10% as well as the life span for equipment from 3 years to 10 years. Also, PLWHA utilisation will be varied using 5% to 10% higher and lower to determine the unit cost variations.

### Process evaluation (qualitative)

A process evaluation will be conducted to understand the fidelity of the delivered ExtraCECI compared with our completed Template for Intervention Description and Replication checklist.^52^ The process evaluation will also clarify causal mechanisms and identify any facilitators or barriers to implementation as well as contextual factors linked to outcomes.^53^ The process evaluation will use data from post-trial qualitative interviews to explore the mechanisms of actions outlined in figure 2. Post-trial interviews will be conducted with PLWHA who received ExtraCECI sampled from at least five clinics (n=30) and HCP who delivered ExtraCECI and their managers (n=20), who will be purposely sampled from the main trial ensuring diverse characteristics, particularly gender, occupation and HIV management. These participants will be interviewed for 40–60 min following a semistructured guide. The interview data will be collected using digital encrypted audio recorders with notes taken as appropriate.

**Figure 2 F2:**
[figure not shown]
Logic model of ExtraCECI - Extra Community-based Enhanced Care Intervention.

The recordings will be transferred onto a password-protected laptop for transcription, and the audio files subsequently deleted from the recorder. Interviews will be transcribed verbatim and translated into English where necessary. Anonymised transcripts will then be imported into NVivo (hosted by ENU) for thematic analysis. The stages of Clarke *et al*^54^ thematic analysis will be followed: familiarisation, generating codes, constructing themes, reviewing themes, and producing the findings. Transcripts will be analysed using deductive-inductive combination (hybrid approach) in thematic analysis proposed by Clarke *et al*^54^ to thoroughly understand ExtraCECI fidelity, implementation and impact. Data will be reported in line with the Consolidated Criteria for Reporting Qualitative Research checklist.^55^ The data obtained will complement the trial data to help identify the contexts and mechanisms that lead to positive outcomes in the trial.

### Joint trial steering committee and data monitoring committee

Due to the low risk profile of the ExtraCECI intervention, a combined steering and data monitoring committee (DMC) will be sought. Therefore, a trial steering committee (TSC) will be convened to provide overall supervision of the trial, ensuring its conduct is in accordance with the protocol and relevant regulations for trial safety. Within the TSC, a smaller DMC will monitor adverse and serious AEs related and unrelated to the trial. The committee will consist of an independent chair and at least two other independent members including a statistician and two context and subject expert, and one PPI, along with the PI, the trial manager and representative from the clinical trials unit. Other study collaborators may also attend the meeting at the discretion of the Chair. The TSC/DMC will meet two times a year to discuss progress of the trial, or more often as appropriate. The role of this committee will also include the review of all serious AEs, and the AEs which are thought to be treatment-related and unexpected.

### Trial management

The day-to-day management of the trial will be undertaken by the trial management group (TMG), which will be chaired by the principal investigator (PI) and will include the trial coordinator, local PIs, coinvestigators and trial statisticians. Monitoring the conduct of the trial and related activities (including the health economic evaluation and process evaluation) will be provided by the TSC. The TSC will include three/four independent experts whose responsibilities will include advising the TMG on any trial management, data management/analysis, ethics and safety monitoring. The trial is being sponsored by Edinburgh Napier University (ENU). A representative of the Sponsor and funder will be invited to attend the TSC meetings.

## Ethics and dissemination

### Research ethics approval

The trial protocol was approved by the ENU School of Health and Social Care Research Integrity Committee (REF: SHSC3681836) and the Ghana Health Service Ethics Review Committee (GHS-ERC:010/07/24). The trial will be conducted according to the approved study protocol and following GCP guidelines and all study participants will sign the consent form (see online supplemental appendix 1) prior to participation. Any substantial deviations from the protocol will be sent to the regulatory authorities for prior review and approval. Appropriate protocol is in place to support any psychological distress experienced by participants including a distress protocol developed to guide researchers in the support process and possible onward referral for further management. The assessment of the trial AE will be conducted by the delegated clinical psychologist who becomes aware of the event and supported by HCP.

### Dissemination

The trial protocol, the trial results, intervention manual and cost-effectiveness results will be published in peer-reviewed open-access journals. Results will also be disseminated via study websites, policy briefs, blogs, social media and at scientific conferences.

### Capacity building

A capacity strengthening needs assessment of the study team with particular focus on development of early career researchers will be undertaken to inform a capacity strengthening plans and ensuring it is contextually appropriate and relevant. Furthermore, capacity building activities will focus on meeting the practice and research gap in PCC by working in collaboration with the Ghana College of Nurses and Midwives, the Nursing and Midwifery Council and other HCP registration bodies to adopt ExtraCECI training as a CPD course for all registered HCP. This will serve as the starting point for bridging the PCC skills gap among HCP. Also, there are plans to build capacity around the conduct of clinical trials by exploring existing resources towards the development of an SOPs for a potential centre for clinical trials at the UoG. The study will also explore and discuss the potential for a postgraduate degree programmes or modules in clinical trials and health statistics as a starting point. The study will use existing links to facilitate engagement with local and global policy-makers to enhance PCC for PLWHA.

